### 2.6. Variables

All study variables will be recorded in a pseudonymized case report form developed specifically for the VOICE-DEP study. Variables will be classified into: (i) baseline variables collected only at V0, and (ii) longitudinal visit variables collected at V0, V1, V2, V3 and V4 in patients with depressive disorder.

Exposure variable: The main exposure variable is the medical diagnosis of moderate or severe unipolar depressive disorder, with or without psychotic symptoms, according to the predefined ICD-10 categories included in the protocol.

Primary outcome variables: The primary outcome variables are the standardized voice recording and the multimodal speech- and speech-derived variables extracted from the recorded clinical interview. These variables will be grouped into acoustic, paralinguistic and linguistic domains.

Clinician-rated and self-reported symptom variables: At each study visit, depressive symptom severity and global clinical status will be assessed concurrently with the voice recording using the MADRS, the Clinical Global Impression scale (CGI), and the Patient Health Questionnaire-9 (PHQ-9). These variables will provide the clinical reference outcomes for cross-sectional and longitudinal analyses. Psychotic depression, operationally defined by an ICD-10 diagnosis of F32.3 or F33.3, will be recorded as a binary clinical variable. The same clinician-rated and self-reported assessments will also be conducted in healthy controls at baseline (V0) to identify possible subthreshold symptoms.

Baseline and longitudinal variables: Baseline variables collected at V0 will include demographic, anthropometric, clinical and contextual information, including psychiatric and medical history, substance use, stressful life events, and previous depressive episodes. Longitudinal variables collected across visits will include recording traceability variables, symptom scales, pharmacological treatment variables, psychotherapy variables and neurostimulation-related variables.

Metadata related to the recording process, including pseudonymized audio identifiers and recording incidents, will also be documented for traceability and quality control purposes.

The complete list of study variables operationalized in the VOICE-DEP case report form is summarized in Table 2. The list of multimodal voice- and speech-derived variables is summarized in Table 3.

**Table 2 pone.0353827.t002:** Study variables recorded in the VOICE-DEP case report form and assessment schedule.

Domain	Description	Assessment visits
Participant identification	Participant category (patient or control), study code, and visit date	V0–V4 in patients; V0 in controls
Sociodemographic and anthropometric baseline variables	Sex, age, marital status, place of residence, birth order in the sibship, height, weight, body mass index, body surface area, educational level, childcare responsibilities, caregiving responsibilities for dependent relatives, religious belief, community religious practice, and social relationships	V0 only
Lifestyle, family history and contextual baseline variables	First-degree family psychiatric history, toxic habits, tobacco, alcohol, cannabis, cocaine, amphetamine and other substance use, physical activity, diet pattern, complementary or alternative treatments and specific prescribed diets, pharmacogenetic or pharmacodynamic isoform information when available, employment status, night work, acute and chronic stressful life events, and current and lifetime traumatic events	V0 only
Clinical baseline variables	Principal diagnosis according to ICD-10 depressive categories, psychiatric comorbidities, medical comorbidities, previous suicidal ideation, previous suicidal behavior, previous self-harm, duration of the current episode, time since initial diagnosis, and number of previous depressive episodes	V0 only
Recording and audio traceability variables	Whether the voice recording was obtained, pseudonymized audio file identifier, presence of recording incidents, and type of incident (patient need, clinical need, technical problem, others)	V0–V4 in patients; V0 in controls
Clinician-rated and self-reported symptom variables	Depressive symptom severity assessed with MADRS, global clinical impression assessed with CGI, and self-reported depressive symptom burden assessed with PHQ-9	V0–V4 in patients; V0 in controls
Pharmacological treatment variables	Pharmacological treatment received, including total daily dose in mg/24h, dosing interval, administration time, and duration of treatment at the recorded dose	V0–V4 in patients
Non-pharmacological treatment and psy-chotherapy variables	Sleep hygiene measures, diet pattern, regular physical activity, discontinuation of toxic habits, psychotherapy attendance, psychotherapy type, and psychotherapy frequency	V0–V4 in patients
Neurostimulation variables	Receipt of electroconvulsive therapy in the current episode, type of electroconvulsive therapy, and other neurostimulation treatments	V0–V4 in patients

**Table 3 pone.0353827.t003:** Multimodal voice- and speech-derived variables predefined in the VOICE-DEP protocol.

Domain	Variable/ group of variables	Operationalization/ measurement
Acoustic	Pitch	F0 mean, standard deviation and range (Hz).
	Energy/ intensity	Mean and standard deviation (dB).
	MFCCs	Coefficients 1–13 summarized by mean and standard deviation.
	Harmonic-to-noise ratio	dB.
	Jitter	Percentage (%).
	Shimmer	Percentage (%).
	Spectral descriptors	Spectral centroid, roll-off and slope (Hz or normalized units).
	Formants	F1–F3 mean frequency and bandwidth (Hz).
	Spectral/ prosodic entropy	Dimensionless entropy index.
	Embedding-based acoustic features	High-dimensional vector representations derived from pretrained models (e.g., Wav2Vec2, HuBERT).
Paralinguistic	Speech rate/ articulation rate/ pause duration	Words per second and pause duration in seconds.
	Prosodic range	F0 and intensity variability (Hz, dB, or coefficient of variation).
	Pause ratio	Silence-to-speech proportion (0–1 or %).
Linguistic	Sentiment polarity	Continuous score from −1 to +1.
	Negative emotional word ratio	Percentage (%) of negatively valenced words.
	First-person singular pronouns	Percentage (%) or frequency per 100 words.
	Lexical diversity	MTLD, Honor´e and type-token ratio.
	Word count/ mean sentence length	Number of words and words per sentence.
	Lexical sentiment variance	Standard deviation of sentiment scores.
	Lexical coherence/ cohesion	Cosine similarity based on semantic embeddings.
	Contextual text embeddings	High-dimensional representations extracted from a pretrained open-weight language model.

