Psychotic status will be considered as a potential confounder and included as a binary covariate when the sample permits stable estimation. Sensitivity analyses excluding patients with psychotic depression will be performed, while subgroup comparisons will be considered exploratory.

Regularized logistic regression will be the primary classification model, with a linear support vector machine and random forest models used for comparison. Missing data, including their frequency, pattern, and documented reasons, will be reported by variable and visit. Mixed-effects models will include a participant-specific random intercept, time as a fixed effect, and selected time-varying covariates; a random slope for time will be considered if supported by the data. The Benjamini–Hochberg procedure will control the false discovery rate within each feature family, and feature selection and hyperparameter tuning will be performed within each training partition.

Because repeated recordings from the same patient are not independent, all longitudinal analyses, predictive modeling and validation procedures will use participant-level data splitting and account for within subject correlation, in order to preserve the independence of training and test data. Specifically, all recordings from the same participant will be assigned exclusively to either the training or the test partition, in order to reduce optimistic bias due to repeated observations from the same individual and avoid information leakage. In this context, Leave-One-Group-Out cross-validation will be used as an appropriate validation framework for grouped repeated-measures data.

To improve clinical interpretability, feature attribution analyses will be performed using Shapley-based methods, including SHAP values where applicable. These analyses will help identify which acoustic, paralinguistic, and linguistic signals contribute most strongly to model predictions and will support the interpretation of the relative importance of different multimodal domains. No imputation for missing data will be applied. To maximize the data collection, quality control reviews will be conducted after every visit. A flexible time-window for visits and periodic reminder phone calls will be planned to reduce the risk of follow-up losses.

All analyses will be performed using Python v3.x or equivalent validated statistical software. Statistical significance will be considered at a two-sided threshold of p < 0.05.

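### Psychotic status appears to be recorded only at V0, so psychosis that resolves or emerges during the 120 days is only partly controlled in the within-patient analyses

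*Protocol article*

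**What the plan says.** Section 2.6 derives psychotic status from the diagnosis code: "Psychotic depression, operationally defined by an ICD-10 diagnosis of F32.3 or F33.3, will be recorded as a binary clinical variable". In Table 2 that code belongs to the clinical baseline block, which begins "Principal diagnosis according to ICD-10 depressive categories, psychiatric comorbidities, medical comorbidities" and is scheduled at V0 alone.

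Nothing collected later carries the same information. Section 2.6 lists the follow-up variables: "Longitudinal variables collected across visits will include recording traceability variables, symptom scales, pharmacological treatment variables, psychotherapy variables and neurostimulation-related variables". The V0–V4 symptom row of Table 2 holds three scales and nothing else: "Depressive symptom severity assessed with MADRS, global clinical impression assessed with CGI, and self-reported depressive symptom burden assessed with PHQ-9".

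One feature of the text points the other way. The sentence that defines psychotic depression sits in a paragraph that opens "At each study visit, depressive symptom severity and global clinical status will be assessed concurrently with the voice recording".

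Section 2.7 then gives the variable two roles. The first is adjustment: "Psychotic status will be considered as a potential confounder and included as a binary covariate when the sample permits stable estimation". The second is exclusion: "Sensitivity analyses excluding patients with psychotic depression will be performed, while subgroup comparisons will be considered exploratory". The longitudinal model is outlined as follows: "Mixed-effects models will include a participant-specific random intercept, time as a fixed effect, and selected time-varying covariates". Change-score approaches are allowed as well. Treatment is the only covariate that the section names as time-varying.

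**The concern.** Secondary objectives ii and iv (section 2.1) ask whether speech changes as severity changes within the same patient. What can distort that association is a third factor that also changes within the patient. If psychosis affects speech and clears as the MADRS score falls, its clearing will look like a link between voice and severity. A patient coded F32.3 at V0 whose psychosis has cleared by V2 would still be coded psychotic at V2 to V4. A patient who becomes psychotic after V0 would stay coded as not psychotic.

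At stake is what the longitudinal report can claim. It could say that psychotic status was adjusted for when only its baseline value was. This is also a gap in data collection: no later analysis plan can enter a visit-level variable that was not recorded. Recruitment has been open since 21 May 2026 (section 2.10).

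**Working it through.** **The plan's own figure.** The protocol gives no number on this point. Its one computed figure is the detectable d of about 0.70 for 25 against 50 (section 2.4). It reproduces: (1.960 + 0.842) × √(1/25 + 1/50) = 0.686 with the normal approximation and 0.695 with the t distribution. Nothing below depends on it.

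**Step 1: algebra.** Let the voice feature of patient i at visit t be y_it = a + b·x_it + g·P_i0 + d·t + u_i + e_it, where x is severity and P_i0 is the V0 flag.

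- *Purely within-person estimator.* Subtracting each patient's mean turns the flag into P_i0 − P_i0 = 0. Its term vanishes and b is the same with or without it.
- *Random-intercept model.* Only a fraction θ of the patient mean is subtracted, with θ = 1 − √(σe²/(σe² + 5σu²)). The flag survives with weight 1 − θ and adjusts the between-patient part of b.
- *Change score V4 − V0.* The confounder is P_i4 − P_i0. The flag is a proxy for it and absorbs the difference in mean change between patients who were and were not psychotic at V0.

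**Step 2: illustrative simulation.** The protocol gives no rates, so all of these inputs are assumptions: 200,000 patients, 5 visits, 30% psychotic at V0, a true severity effect on voice of 0, psychosis shifting both severity and voice by 1 unit, random-intercept SDs of 1 and residual SDs of 0.7. With these values θ = 1 − √(0.49/5.49) = 0.70.

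The monthly probabilities of resolution and onset are A: 0.35 and 0.02; B: 0.35 and 0; C: 0.15 and 0.05. Entries are the estimated severity slope, so any departure from 0 is bias.

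| Model | Scenario | No covariate | V0 flag | Share removed | Visit-level status |
|---|---|---|---|---|---|
| Within-person | A | 0.122 | 0.122 | 0% | 0.001 |
| Within-person | B | 0.096 | 0.096 | 0% | 0.001 |
| Within-person | C | 0.122 | 0.122 | 0% | −0.001 |
| Random intercept | A | 0.113 | 0.105 | 0.008/0.113 = 7% | 0.001 |
| Random intercept | B | 0.089 | 0.081 | 0.008/0.089 = 9% | −0.001 |
| Random intercept | C | 0.121 | 0.108 | 0.013/0.121 = 11% | −0.001 |
| Change score | A | 0.190 | 0.073 | 0.117/0.190 = 62% | −0.001 |
| Change score | B | 0.158 | 0.042 | 0.116/0.158 = 73% | −0.002 |
| Change score | C | 0.196 | 0.144 | 0.052/0.196 = 27% | 0.002 |

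If psychosis never changes, the V0 flag is enough: the random-intercept bias goes from 0.038 to 0.001.

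**Step 3: the planned exclusion.** Dropping patients psychotic at V0 from the random-intercept model takes the slope from 0.113 to 0.032 (A), from 0.089 to 0.000 (B, no onset) and from 0.121 to 0.070 (C). It clears the bias from resolution and leaves the bias from new onset.

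**Step 4: the planned sample size.** A second simulation used 25 patients, 5 visits and 150 datasets per scenario. It assumed 6 patients psychotic at V0, all resolving by V1 to V3, a speech shift of 0.8, intercept and residual SDs of 0.7, and no true MADRS effect. Mean MADRS at V0 was 38 (psychotic) or 30 (other), falling 5.5 or 4 points per visit. The model separated within- and between-person MADRS. With time in the model, false positives at a nominal 5% were 9% with the V0 flag and 4% with visit-level status. With 150 datasets the 9% has a 95% Monte Carlo interval of about 5 to 15%. With 3 psychotic patients the V0-flag rate with time in the model was about 3%, so there was no inflation.

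**The case against.** The strongest reply has four parts.

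- **Fixing at V0 is not stated.** The defining sentence stands in a paragraph about every visit, section 2.3 has relevant clinical changes documented at follow-up, and section 2.7 leaves room for selected time-varying covariates. This stands in so far as the point must be put as an inference. But section 2.6 presents Table 2 as covering the complete list of case report form variables, and the table shows no visit-level source. If recording at each visit is intended, Table 2 needs correcting.
- **The flag is not useless.** A reader might infer that it removes none of the confounding. That is exact only for a purely within-person estimator. The protocol names random-intercept and change-score models and states no within/between split, and in those models the flag removes part of the bias.
- **The exclusion analysis already helps.** This stands for resolution. It does not stand for onset after V0, and it costs patients from a group of 25.
- **Visit-level adjustment may over-adjust.** Psychosis that clears with the episode may be part of the severity being tracked, since the eligible codes F32.3 and F33.3 place it within severe episodes. Section 2.7 also makes the covariate conditional on stable estimation. This stands, and it is why adjusted and unadjusted models should appear side by side.

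Two further inferences should be resisted. The second simulation gives a false-positive rate of 21% when time is left out, but section 2.7 requires time as a fixed effect, so that figure does not describe the planned model. And the mention of psychotic symptoms in section 2.8 is a general safety clause, not a forecast that patients will become psychotic during follow-up.

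**Conclusion.** The point holds as a limited gap in data collection. As far as Table 2 shows, psychotic status has one source, the V0 diagnosis code, and cannot follow change within a patient. In the simulated random-intercept model, the form section 2.7 outlines, 89 to 93% of the bias remained after adjustment for the flag (0.108/0.121 to 0.105/0.113). In the change-score model 27 to 73% remained (0.042/0.158 to 0.144/0.196).

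The exact cancellation in a within-person estimator does not depend on the assumed rates. The other magnitudes do: they rest on assumed prevalence, resolution, onset and effect on speech, none of which the protocol gives. The practical effect is negligible if few patients are psychotic and absent if psychosis does not change over follow-up. The affected analyses are secondary. The patient–control comparison at baseline, which serves the primary objective, is not touched.

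**What to change.** - **Table 2:** add one item for patients to the V0–V4 clinician-rated row: psychotic symptoms present at this visit (yes/no), judged in the interview already held.
- **Section 2.7:** where the sample permits stable estimation, report the patient-only longitudinal models with and without this item as a time-varying covariate, and say that both are shown because current psychosis may be part of severity.
- **V0 ICD-10 code:** keep it for description, for patient–control models and for the exclusion sensitivity analysis, and state that it adjusts for baseline psychotic status only.

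The cost is one tick box per patient visit and one extra model. Values for visits already completed would have to come from clinical notes. The consent form covers record access when study objectives require it (section 2.9), but such values are less standardised and should be flagged as retrospective.

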### 2.2. Study population and participant characteristics

The study will include two groups: (1) patients with a medical diagnosis of moderate or severe unipolar depression and (2) healthy control participants without a personal history of depression or any other psychiatric disorder.

Inclusion criteria for patients are: Age 18 years or older; Native Spanish speakers or individuals with sufficient fluency in Spanish to maintain a clinical interview; Capacity to understand study procedures and provide written informed consent, according to the investigator’s judgement; Medical diagnosis of moderate or severe unipolar depression, with or without psychotic symptoms, according to ICD-10 categories: moderate depressive episode (F32.1), severe depressive episode without psychotic symptoms (F32.2), severe depressive episode with psychotic symptoms (F32.3), recurrent depressive disorder, current episode moderate (F33.1), recurrent depressive disorder, current episode severe without psychotic symptoms (F33.2), or recurrent depressive disorder, current episode severe with psychotic symptoms (F33.3), regardless of whether the patient receives psychotherapeutic, pharmacological or neurostimulation treatment, or chooses not to receive active treatment while remaining under clinical follow-up.

Exclusion criteria for patients are: Severe neurological disorders affecting speech production or cognitive function, such as severe dementia; Severe voice or speech disorders unrelated to depression that prevent completion of the clinical interview through verbal language; State of intoxication due to substance use at the time of assessment; Other severe medical conditions interfering with study participation or speech production.

Inclusion criteria for healthy controls are: Age 18 years or older. Exclusion criteria for healthy controls are: Personal history of depression or any other psychiatric disorder; Severe neurological disorders affecting speech production or cognitive function, such as severe dementia; Severe voice or speech disorders unrelated to depression that prevent completion of the clinical interview through verbal language; State of intoxication due to substance use at the time of assessment; Other severe medical conditions interfering with study participation or speech production.

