### 2.7. Statistical and analytical plan

The analytical strategy of the VOICE-DEP study is designed to support the primary and secondary objectives of the protocol while ensuring methodological transparency, reproducibility, and robustness. In accordance with the study design, the analysis will address three complementary dimensions: (i) descriptive characterization of the study sample and extracted variables, (ii) exploratory cross-sectional association and discrimination analyses between patients with depressive disorder and healthy controls, and (iii) longitudinal intra-individual modeling of changes in voice- and speech-derived variables in relation to clinical evolution.

First, a descriptive analysis will be performed for all study variables recorded in the case report form. Quantitative variables, including acoustic, paralinguistic, and linguistic features, will be summarized using means and standard deviations or medians and interquartile ranges, as appropriate according to their distribution. Qualitative variables will be described using absolute frequencies and percentages. This descriptive phase will include both baseline variables collected at V0 and longitudinal variables collected across repeated visits in patients. Age, sex, educational level and available socioeconomic-related variables will be compared between groups and considered as covariates in adjusted or sensitivity analyses when relevant imbalance is observed and the sample size permits stable estimation.

Second, the association between continuous voice- and speech-derived digital biomarkers and clinical severity measures will be explored using Pearson or Spearman correlation coefficients, depending on distributional assumptions. These analyses will focus on the relationship between multimodal voice-derived variables and clinician-rated depressive symptom severity measured with the MADRS, global clinical status measured with the CGI, and self-reported depressive symptom burden measured with the Patient Health Questionnaire-9 (PHQ-9).

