For diagnostic discrimination between patients and healthy controls, classification models will be developed and evaluated. The area under the receiver operating characteristic curve (AUC) will be used as the principal performance metric, and additional measures such as odds ratios and their corresponding 95% confidence intervals will be reported where applicable. These analyses will be interpreted as exploratory because the study is a pilot methodological validation study rather than a definitive diagnostic accuracy trial.

Third, a systematic comparison between unimodal and multimodal approaches will be conducted. Unimodal models will include models based exclusively on audio-derived features or text-derived features, whereas multimodal models will combine acoustic, paralinguistic, and linguistic information. This comparison is intended to quantify the added value of multimodal integration beyond individual feature domains and is directly aligned with one of the predefined secondary objectives of the study.

Embedding-based acoustic features and contextual text embeddings will be evaluated exploratorily because previous studies suggest that they may capture clinically relevant patterns beyond predefined features [8,10,12,13]. Given their high dimensionality and limited interpretability, they will not constitute the primary analytical approach. Model specifications and extraction procedures will be fully documented to ensure transparency and reproducibility.

Longitudinal analyses will be used to evaluate the evolution of voice- and speech-derived digital biomarkers over time and their association with changes in depressive symptom severity and global clinical status. Because repeated assessments are obtained in the patient group at V0, V1, V2, V3, and V4, these analyses will account for within-subject correlation. Mixed-effects models and, where appropriate, finite-difference or change-score approaches will be used to examine intra-individual trajectories and their relationship with variation in MADRS, CGI, and PHQ-9 scores, as well as with relevant treatment-related variables. Treatment exposure and changes during follow-up will be included, where feasible, as time-varying covariates in the mixed-effects models. Treatment-specific analyses will be considered exploratory and will not be interpreted causally.

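### The baseline patient-control contrast cannot separate depression from its treatment: patients enter on any treatment, treatment is analysed only longitudinally, and controls' medication is not collected

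*Protocol article*

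**What the plan says.** Section 2.2 makes patients eligible "regardless of whether the patient receives psychotherapeutic, pharmacological or neurostimulation treatment, or chooses not to receive active treatment", and section 2.1 recruits from both inpatient and outpatient care. For controls, section 2.2 gives "Inclusion criteria for healthy controls are: Age 18 years or older" and then "Exclusion criteria for healthy controls are: Personal history of depression or any other psychiatric disorder", followed by neurological, voice, intoxication and medical exclusions. Medication is not a criterion in either group.

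On data collection, section 2.6 states: "The complete list of study variables operationalized in the VOICE-DEP case report form is summarized in Table 2". In that table the pharmacological row reads "Pharmacological treatment received, including total daily dose in mg/24h, dosing interval, administration time, and duration of treatment at the recorded dose V0–V4 in patients". The non-pharmacological and neurostimulation rows are likewise limited to patients. Rows meant to cover controls, such as the symptom scales and audio traceability, say so explicitly.

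On analysis, section 2.7 says of the group comparison: "Age, sex, educational level and available socioeconomic-related variables will be compared between groups and considered as covariates", when imbalance is seen and numbers permit. It also names psychotic status as a potential confounder. Treatment appears in the longitudinal part: "Treatment exposure and changes during follow-up will be included, where feasible, as time-varying covariates in the mixed-effects models". Section 3.1 concedes that changes in speech cannot be fully separated from treatment effects. It makes no such statement about the baseline comparison.

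**The concern.** Discriminating patients from controls is part of the primary objective (section 2.1), and section 2.6 names the diagnosis as the main exposure. Treatment at V0 can be common among patients and should be rare among controls, who have no psychiatric history. Any effect of treatment on speech rate, pauses, jitter, shimmer, harmonic-to-noise ratio or F0 range would then appear in the contrast as if it belonged to depression, and would feed the AUC.

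The plan recognises that treatment may act on speech, since it models treatment over time, but it does not carry this over to the baseline comparison. The gap in controls' data is a separate matter. A later analysis plan can add an analysis but cannot recover a variable that was never collected, and section 2.10 shows recruitment open since 21 May 2026.

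**Working it through.** **The plan's own figure.** Section 2.4 gives a detectable d of about 0.70 for 25 versus 50, two-sided 0.05, 80% power. Normal approximation: (1.960 + 0.842) × √(1/25 + 1/50) = 0.686. With the t distribution it is 0.695, and power at d = 0.70 is 0.805. The figure reproduces; nothing here is an arithmetic error.

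**Inputs for the bias.** From the document: 25 patients, 50 controls, two-sided 0.05. Assumed, because the document gives no value: the share m of patients on a treatment that affects speech, and its effect δ in SD units. Controls are taken as untreated and depression itself as having no effect on the feature.

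**Formulas.** Apparent difference d = m × δ. Non-centrality = d / √(1/25 + 1/50), with 73 degrees of freedom. Single-feature AUC = Φ(d/√2).

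| m | δ (SD) | d | nominal p<0.05 | AUC |
|---|---|---|---|---|
| 0.60 | 0.3 | 0.18 | 11% | 0.551 |
| 0.80 | 0.5 | 0.40 | 36% | 0.611 |
| 0.80 | 0.8 | 0.64 | 73% | 0.675 |
| 0.95 | 0.8 | 0.76 | 87% (0.865) | 0.705 |

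These treat the patient group as a shifted normal. Simulating the treated/untreated mixture directly changes little: 0.353 and 0.713 for the two middle rows, and a range of 0.115 to 0.863 overall.

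**Effect of the plan's multiplicity rule.** Section 2.7 applies Benjamini–Hochberg within each feature family. Counting the non-embedding acoustic variables in Table 3: pitch 3, intensity 2, MFCCs 26, harmonic-to-noise ratio 1, jitter 1, shimmer 1, spectral descriptors 3, formants 6, entropy 1, total 44. If the affected feature were the only rejection, its threshold would be 0.05/44 = 0.0011, and the middle rows fall from 36% to about 5% and from 73% to about 23%. With more rejections the threshold moves back towards 0.05, so the nominal rates are upper ends. The expected shift d and the AUC do not depend on the testing rule.

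**What a patient-only comparison could show.** Treated versus untreated among 25 patients, two-sided 0.05:

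| untreated patients (assumed) | power, δ = 0.5 | power, δ = 0.8 |
|---|---|---|
| 3 | 12% | 24% |
| 5 | 16% | 34% |
| 10 | 22% | 47% |

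Such a comparison can describe, but it cannot clear a feature of a treatment effect.

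**The case against.** The strongest reply is that the plan does more about treatment than it first appears. Patients' treatment is recorded at V0, section 2.7 promises a description of all case report form variables, the mixed models span V0 to V4, and one secondary objective concerns treatment modality. Discrimination results are labelled exploratory and the markers are called candidates. Open eligibility is a deliberate choice for a real-world pilot, and a V0 sensitivity analysis is something an unseen analysis plan could contain. All of this stands and lowers the weight of the point. It does not meet it: describing the treatment mix does not link it to V0 features or classifier scores, and an exploratory label speaks to precision rather than to what the contrast measures.

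Three stronger readings are tempting, and the documents do not support them.

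- A reader might take 36% or 73% as the study's false-finding rate. Those figures rest on assumed inputs and unadjusted p<0.05, not on the plan's false discovery rate rule.
- A reader might infer that the missing control medication inflates the contrast. The calculation assumes untreated controls, so that gap contributes nothing to it. A control on a sedating drug would more likely resemble treated patients and shrink the difference. Controls' medical comorbidities and substance use do appear in V0 rows not limited to patients, so such a control is not wholly hidden, but comorbidity is not medication.
- A reader might want features that track treatment removed from the candidate markers. Treatment follows severity and psychosis, so a true severity marker could track it too, and power is too low to sort features this way.

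**Conclusion.** The point holds in a limited form. As written, the V0 contrast and AUC are attributed to the diagnosis with treatment left unaddressed, and the groups cannot be compared on medication because controls' medication is not collected. The magnitude is unknown. Under 60–95% treated and an effect of 0.3–0.8 SD, the shift is 0.18–0.76 SD; its upper part is of the same order as the 0.70 SD the design can detect. If few patients are treated at V0, or treatment hardly affects these features, the bias is small. The protocol does not say that the classifier uses only V0 recordings; if follow-up recordings enter, treatment exposure in the patient class can only be wider. The change is worth making, and making early, since each control assessed without the entry may be lost for this purpose.

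**What to change.** 1. Change the visit entry of the Table 2 pharmacological row to V0–V4 in patients plus V0 in controls. Run a sensitivity analysis of the V0 contrast without controls on psychotropic or sedating drugs.
2. Add a descriptive, patient-only V0 comparison of the selected features and the out-of-fold classifier scores by treatment status. Give confidence intervals and show MADRS and psychotic status alongside. State that it is imprecise, that treatment follows severity, and that a null result does not rule out a treatment effect. Do not enter treatment in the patient-control model, where it nearly coincides with group, and do not use this comparison to remove or reclassify features.
3. Extend the treatment limitation in section 3.1 to the baseline contrast, and state that the V0 AUC describes depression as treated in this hospital versus healthy controls.

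The cost is one more case report form entry at the controls' single visit, wide intervals in the patient-only comparison, and a more cautious claim. No clinical procedure changes.
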